### Procedure for unblinding if needed {17b}

Each investigator trained for the trial and listed in the delegation log has an individual password protected access to the eCRF, where the information regarding the patient’s allocation is available.

### Data collection and management

#### Plans for assessment and collection of outcomes {18a}

The following parameters will be recorded at the start of the trial: medical history including concomitant diseases (particularly chronic inflammatory disease, cardiovascular disease, and smoking habits), medication including systemic anticancer treatment, physical examination, age, date of birth, gender, body height and body weight, performance status (ECOG-PS [13]), tumor side (affected breast) and location, stage, histology, hormone receptor status, HER2 status, Ki-67 labeling index, triple-negativity, planned total radiation dose, dose per fraction, number of fractions, radiation boost, treatment volume (breast alone, chest wall alone, breast plus lymph nodes, chest wall plus lymph nodes), radiation technique, deep-inspiration breath hold (DIBH) technique, and pain score including the intake of analgesics.

The following parameters will be assessed during the course of the trial:1. Radiation dermatitis: Assessed by an observer different from the person who performs the routine visit of the patient at the start of, weekly during, and at the end of radiotherapy (CTCAE v5.0) [11] .2. Pain (skin within radiation fields): Assessed prior to, weekly during, and at the end of radiotherapy (visual analogue scale). Furthermore, intake of analgesics will be documented.3. Adverse events other than radiation dermatitis will be assessed on an ongoing basis (CTCAE v5.0) [11].4. Eastern Cooperative Oncology Group (ECOG): Evaluated prior to and at the end of radiotherapy [13].5. Physical examination: Performed prior to, weekly during radiotherapy, and at the end of radiotherapy.6. Patient satisfaction with the reminder app, its impact on the use of health technology, and benefit from support (coaching) by staff members: Assessed with specific questionnaires at the end of radiotherapy.

The timeline of trial procedures and assessments is given in Figure 1.

### Plans to promote participant retention and complete follow-up {18b}

The last day of radiotherapy is also the end of the follow up period. Patients are seen at least five days per week by medical staff members. Thus, it is unlikely that patients will be lost to follow up.

### Data management {19}

All data relating to patients will be recorded in a pseudonymous way. Each patient will be identifiable only by the unique patient number, year of birth and gender. A patient identification list will be kept only in the relevant trial centers and not forwarded to the sponsor. Data collection will be done using eCRFs. The data will be handled according to the General Data Protection Regulation (GDPR). The data will be included in one data base and analyzed in accordance with a pre-defined statistical analysis plan (SAP). Originals of key trial documents including documentation sheets will be kept at the trial headquarters (sponsor responsible for the trial) for at least 10 years after the final report. The principal investigator/head of the trial center will keep all administrative documents, the patient identification list, signed informed consent forms, copies of the documentation sheets, and general trial documentation (protocol, amendments) for the abovementioned period. Original patient data must also be kept for the length of time stipulated for the trial centers, but not for less than 10 years.

### Confidentiality {27}

Data will be collected in accordance with the regulations set out in the Data Protection Act. All findings from the clinical trial will be stored on electronic data storage devices and treated with utmost confidentiality. Organization measures have been taken in order to prevent the data from being communicated to unauthorized persons. Patients will only be identified via their individual patient numbers throughout the entire documentation and evaluation phase and their full name will not be used.

### Plans for collection, laboratory evaluation and storage of biological specimens for genetic or molecular analysis in this trial/future use {33}

Laboratory evaluation and storage of biological specimens for genetic or molecular analysis in this trial or for future use are not planned.

### Statistical methods

#### Statistical methods for primary and secondary outcomes {20a}

All data recorded in the eCRFs describing the study population and toxicity will be analyzed descriptively. Categorical data will be presented in contingency tables with frequencies, percentages and their 95% confidence intervals. Continuous data will be summarized with at least the following: frequency (n), median, quartiles, mean, standard deviation (standard error), minimum and maximum. Number of patients with protocol deviations and listings describing the deviations will be provided. In general, chi-square tests will be used to compare percentages in a two-by-two contingency table, replaced by Fisher´s exact test if the expected frequency in at least one cell of the associated table is less than 5. Stratified two-by-two contingency tables will be analyzed using Cochran-Mantel-Haenszel tests. Logistic regression models serve as multivariable methods for binary endpoint data. Comparison of ordinal variables between treatment arms will be performed using the asymptotic Wilcoxon-Mann-Whitney test, replaced by its exact version in case of ordinal categories with small number of categories and/or sparse data within categories. Any shift in location of quantitative variables between study groups will be performed with Wilcoxon-Mann-Whitney tests. Time-to-event data will be analyzed by Kaplan-Meier methods, when merely non-informative censoring occurs. For statistical comparison, the log rank-test will be provided supplemented by multivariate Cox proportional hazards models. The data analysis will be performed according to the SAP finalized prior to database lock and prior to any statistical analysis.

### Interim analyses {21b}

An interim analysis is not planned at this stage.

### Methods for additional analyses (e.g. subgroup analyses) {20b}

Elderly patients aged ≥65 years will be compared to younger patients aged <65 years to identify potential differences between both age groups and the need for support regarding the use of the reminder app. Standard statistical tests serve as a tool for exploratory comparison of age groups.

### Methods in analysis to handle protocol non-adherence and any statistical methods to handle missing data {20c}

The Full Analysis Set includes all randomized patients who have started either therapy with arm A or with arm B and provide any data on the primary endpoint. The Full Analysis Set will be analyzed according to the Intention-to-Treat principle, i.e., patients will be analyzed in their initial group of randomization.

The Per Protocol Set includes all patients of the Full Analysis Set excluding patients in case of administration of less than 75% of the planned radiation dose if the reason for discontinuation was any other than death or unacceptable toxicity and/or in case of >50% missing data regarding the primary study endpoint. All patients in the Per Protocol Set will be analyzed within their group of actual treatment received.

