### Intervention description {11a}

#### Standard skin care

In both the experimental arm (A) and the control arm (B) standard skin care has to be performed by the patient from the start of radiotherapy. The patients are supposed to perform the skin care four times a day. Standard skin care may vary at the participating centers. At the University of Lübeck, it includes fatty cream with 2-10% urea (fatty cream alone, if patients do not tolerate urea) and, in case of pruritus, addition of mometasone furoate cream.

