#### Reminder App

In addition, patients of Arm A are supported by a Reminder App, which is developed by the professional company Nextlabel OHG from Lübeck. The purpose of the app is to remind the patients in an intuitive, unobtrusive and supportive way to perform skin care. By default, patients are reminded four times a day, but they will also be able to define a notification schedule that best suits their personal needs. The patients may postpone each required care procedure for up to 2 hours. With each procedure, the patients are guided through the skin care with simple and self-explanatory illustrations. To increase the patients’ motivation, they will additionally earn points for regular and punctual performed care procedures. The patients receive a hand-out including instructions how to properly perform skin care, but they can also find an information page within the application that includes similar instructions.

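### Grouping the Per Protocol Set by treatment actually received, with no rule on app use, gives up randomization and can bias this supportive comparison towards the app

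*Protocol article*

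**What the plan says.** The section on non-adherence and missing data {20c} defines two analysis sets and groups them differently.

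- **Full Analysis Set.** It contains "all randomized patients who have started either therapy with arm A or with arm B and provide any data on the primary endpoint". On grouping: "The Full Analysis Set will be analyzed according to the Intention-to-Treat principle, i.e., patients will be analyzed in their initial group of randomization".
- **Per Protocol Set.** It is the Full Analysis Set after two exclusions. The first is stated as "excluding patients in case of administration of less than 75% of the planned radiation dose", unless the patient stopped because of death or unacceptable toxicity. The second applies "in case of >50% missing data regarding the primary study endpoint". On grouping: "All patients in the Per Protocol Set will be analyzed within their group of actual treatment received".

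The intervention sections show what separates the arms. On background care: "In both the experimental arm (A) and the control arm (B) standard skin care has to be performed by the patient". On the experimental element: "In addition, patients of Arm A are supported by a Reminder App". The sample size section {14} sets 131 patients per arm within the Full Analysis Set.

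**The concern.** The sentence on the Per Protocol Set prescribes an as-treated comparison, in explicit contrast to the as-randomized one just above it. Patients are then grouped partly by what they did after randomization, and the two groups are no longer comparable by design.

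The risk is specific in this trial. The app is the only difference between the arms, so an Arm A patient who never opens it has in substance had standard skin care alone, which is what Arm B receives. Neither exclusion removes such a patient, and the grouping rule can place her in Arm B. The Discussion argues that better adherence to skin care may lead to less dermatitis. If patients who ignore a reminder are also less diligent with their skin care, the rule moves higher-risk patients out of Arm A and into Arm B.

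At stake is how a per-protocol result would be read. If it is more favourable than the as-randomized result, it could be taken to show that the app works when used, although selection alone can produce that pattern.

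**Working it through.** **The plan's own figure.** For 30% versus 15%, two-sided 5% and 80% power, the usual formula gives 121 per arm, or 134 with continuity correction. Exact enumeration at 131 per arm gives power 0.837 for the uncorrected chi-square test and 0.801 for Fisher's exact test. Then 131/0.98 = 133.7, rounded up to 134, and 2 × 134 = 268. The stated 131 and 268 are consistent and do not depend on the Per Protocol rule.

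**Inputs for the bias check**
- From the documents: n = 131 per arm (section {14}; the Per Protocol exclusions are taken to remove nobody); p0 = 25.4%, the pre-study rate in section {14}; two-sided 5% level.
- Assumed, because the documents give no figure: no app effect, so the true rate is p0 in both randomized arms; a share f of Arm A are non-users; their risk is R times that of Arm A users; all non-users are counted in Arm B.

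**Formulas**
- User risk: u = p0 / (1 − f + fR). This is the as-treated Arm A rate.
- As-treated Arm B rate: pB = (p0 + fRu) / (1 + f).
- Group sizes: nA = 131(1 − f), nB = 131(1 + f).
- Spurious benefit: d = pB − u.
- False significant benefit: Φ((d − 1.96·s0)/s1), with s0 the pooled and s1 the unpooled standard error. The nominal value in this direction is 2.5%.

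**Worked case, f = 20%, R = 1.5**
- u = 0.254/(0.8 + 0.3) = 0.2309; non-user risk 1.5 × 0.2309 = 0.3464.
- pB = (0.254 + 0.2 × 0.3464)/1.2 = 0.2694.
- d = 0.2694 − 0.2309 = 0.0385, or 3.8 points.
- nA = 104.8, nB = 157.2, s0 = 0.0549, s1 = 0.0543.
- (0.0385 − 0.1076)/0.0543 = −1.27, giving about 10.1%.

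**Range at p0 = 25.4%**

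| Non-users in Arm A | R = 0.8 | R = 1.0 | R = 1.5 | R = 2.0 |
|---|---|---|---|---|
| 10% | −0.9 points; 1.6% | 0; 2.5% | 2.2 points; 6.0% | 4.2 points; 11.7% |
| 20% | −1.8 points; 1.2% | 0; 2.5% | 3.8 points; 10.1% | 7.1 points; 24.5% |
| 30% | −2.5 points; 0.9% | 0; 2.5% | 5.1 points; 14.0% | 9.0 points; 35.3% |

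Each cell gives the spurious benefit, then the chance of a false significant benefit. A negative value counts against the app. With only 5% non-users and R = 1.5, the figures are 1.2 points and 4.1%.

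**Sensitivity to the base rate.** At the 30% control rate used for planning, f = 20% and R = 1.5 give 27.3% versus 31.8%, a spurious benefit of 4.5 points. The test then rejects in either direction 12.1% of the time instead of 5%.

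**The case against.** A reader might infer that the protocol orders non-users into Arm B and so manufactures a benefit. The text does not say this. Treatment actually received is undefined and could mean only that the wrong arm was delivered in error. The data listed in section {18a} contain no measure of app use, so on that list the regrouping could not be carried out. The operational definition may also be left to the SAP. This part stands: the reassignment is something the rule permits, not something it states. It does not rescue the sentence, which fixes an as-treated grouping for a supportive analysis in an open-label trial and leaves its meaning to be settled later.

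The direction of bias is conditional too. The table shows no bias at equal risk and a reversed one when non-users have lower risk. Eligibility requires a smartphone and the ability to use it, expected non-compliance is an exclusion criterion, and staff see patients at every session. These make extensive non-use less likely without ruling it out.

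Two further inferences are tempting and are not supported. The first is that the Full Analysis Set has a hurdle for Arm A only. Its start condition is worded for both arms, and skin care begins with radiotherapy in both; an asymmetry appears only if starting is read as installing the app. The second is that a negative primary result is likely because power is low. At the planned 30% versus 15%, 131 per arm gives about 80 to 84%. A value near 55% arises only at 25.4% versus 15%, and the choice of planning rate is a separate question.

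**Conclusion.** The concern holds for the Per Protocol analysis alone. Its grouping rule gives up randomization and, with no definition of treatment received and no criterion on app use, leaves the comparison open to selection by adherence. If 10 to 30% of Arm A are non-users with 1.5 to 2 times the users' risk and are counted in Arm B, an app with no effect would appear to lower dermatitis by about 2 to 9 points, with a 6 to 35% chance of a false significant benefit. These figures rest on assumed non-user shares and risks and show what could happen; they are not a forecast. The primary comparison is protected: the Full Analysis Set is analysed as randomized, the trial is sized on it, and nothing in the article makes the Per Protocol Set the basis of the main conclusion. The sentence should still be changed, because the correction is specific and nearly free.

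**What to change.** Replace the last sentence of section {20c} so that Per Protocol patients are analysed in the arm to which they were randomized, with the same exclusion rules in both arms. State that the analysis is supportive. Make the change in the protocol and carry it into the SAP before database lock.

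Dropping non-users from Arm A alone would not be an adequate substitute. At a 30% rate with f = 20% and R = 1.5 it still leaves a spurious benefit of 30.0 − 27.3 = 2.7 points.

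The cost is one sentence of wording. The downside is that the analysis no longer describes outcomes by actual app use. If that question matters, a complier-average estimate could be added, but only if usable records of app use exist. The article says of Arm A patients that "they will additionally earn points for regular and punctual performed care procedures", which suggests that the app registers procedures. It does not say that individual records are kept or can be linked to trial data, and section {26b} plans no additional data collection. Such an estimate would also need a usage threshold set in advance and the assumption that allocation affects dermatitis only through use of the app. It is therefore optional.

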### Plans to give access to the full protocol, participant level-data and statistical code {31c}

Many details of the study protocol including statistical considerations are available at clinicaltrials.gov. The full protocol and individual participant data will not be shared.

### Oversight and monitoring

#### Composition of the coordinating center and trial steering committee {5d}

The staff of the coordinating center includes the principle investigator, his deputy, and more than ten sub-investigators plus a study nurse/secretary. There is no specific steering committee for this trial. The trial is part of a subgoal of the Interreg-project HeAT including five trials. Senior staff members of the project and network partners involved in the subgoal and the corresponding trials meet twice a year.

#### Composition of the data monitoring committee, its role and reporting structure {21a}

A data monitoring committee is not required, since all patients participating in this trial receive the same anticancer treatment, the same number and type of visits and the same treatment for radiation dermatitis, oral mucositis and other toxicities as they would have received if not participating in the trial.

### Adverse event reporting and harms {22}

#### Assessment and documentation of adverse events

The severity of adverse events should be assessed using the Common Terminology Criteria for Adverse Events (CTCAE), version 5.0 [11]. Otherwise the following, the five-point scale below will be used to describe an adverse event: 1 = mild, 2 = moderate, 3 = severe, 4 = life-threatening, 5 = fatal

The following scale is used to describe the likelihood that the event was caused by the trial treatment:

1 = certain / definite, 2 = probable, 3 = possible, 4 = unlikely, 5 = not related, 9 = not assessable

Serious adverse events and unexpected adverse events must be reported within 24 hours after their detection/onset by fax to the coordinating investigator.

### Frequency and plans for auditing trial conduct {23}

The ZKS Lübeck will conduct on-site monitoring at the German sites according to principles of Good Clinical Practice (GCP) and written SOPs. For initiation, trial sites will be visited on-site. During the trial, sites will be visited at regular intervals depending on recruiting rate and data quality. Informed consent and defined key data will be checked of all patients. The medical file of each patient will be screened for adverse and serious adverse events. Patients’ questionnaires will be checked for their existence. Sites not based in Germany will be monitored according to their corresponding national regulations. No regular audits are planned but may be conducted if necessary. As this trial is not linked to the German pharmaceutical or medicinal product act, inspections of higher federal authorities are not planned.

### Plans for communicating important protocol amendments to relevant parties (e.g. trial participants, ethical committees) {25}

Amendments to the study protocol will be sent to and required approval from the local ethics committee. Only the coordinating principal investigator may carry out changes. If modifications appear required, co-investigators should contact the coordinating principal investigator. In the case of approved modifications of study protocol, all investigators will be informed.

### Dissemination of results and publication policy {31a, 32}

The coordinating principal investigator will strive for dissemination of trial results. Coordinating principal investigator and biostatistician will create a report according to the CONSORT statement, regardless of regular or early trial termination.

Results will be published in peer-reviewed journals and presented at scientific meetings. Reports and publications related to the trial must be coordinated with the biostatistician. Participating centers may use recorded data for additional analyses under their own name, but only after the main results have been published. Any additional or sub-publication requires approval by the coordinating principal investigator. For publications of any kind the study acronym DAI-BREAC must be used.

## Discussion

Adjuvant radiotherapy is an integral part of breast-conserving treatment of breast cancer patients and is also required after mastectomy in case of risk factors regarding loco-regional recurrences [1, 2]. During recent years, hypo-fractionated irradiation with a total dose of 40 Gy administered in 15 fractions of 2.667 Gy on 5 days per week is increasingly used [8, 9]. Ideally, radiotherapy is performed with precision techniques, namely intensity-modulated radiation therapy (IMRT) or volumetric modulated arc therapy (VMAT) [11]. Due to these techniques, the risk of radiation-related toxicities can be reduced. Another option that can help decrease the risks of cardiac or pulmonary morbidity deep-inspiration breath hold technique that is particularly used to treat left-sided breast cancer [14, 15]. Despite the improvement in radiation techniques, treatment-related adverse events still remain a risk in patients irradiated for breast cancer.

A common acute toxicity of radiotherapy for breast cancer is radiation dermatitis [3, 4, 12]. If dermatitis exceeds grade 1, it can be quite painful and have a negative impact on the patients’ quality of life [3]. If it becomes more severe, it may even require an interruption of the radiation treatment. In order to avoid grade ≥2 dermatitis, it is important that the patients perform specific skin care for the radiation fields several times per day, which should be started at the first day of radiotherapy. This may require considerable diligence and self-discipline from the patients. It may be questioned whether patients irradiated for breast cancer could benefit from a mobile application reminding them several times a day to perform their skin care. These reminders may improve the patients’ awareness and compliance. Improved adherence to the recommended skin care protocol may result in less radiation dermatitis.

In a previous retrospective study of our group that included 327 breast cancer patients irradiated in 2022 or 2023, 31.2% of the patients developed grade ≥2 radiation dermatitis [12]. Moreover, several factors showed highly or almost highly significant associations with the occurrence of grade ≥2 dermatitis on multivariate analysis, including history of chronic inflammatory disease (*p*=0.001), history of significant cardiovascular disease (*p*<0.001), smoking history of more than 10 pack years (*p*<0.001), normo-fractionated radiotherapy (*p*<0.001), and administration of a radiation boost (*p*<0.001). These risk factors were considered when designing the current DAI-BREAC trial. This randomized trial compares the rate of grade ≥2 radiation dermatitis with standard skin care plus a reminder app to the dermatitis rate with standard skin care alone in a cohort of 268 patients. If it is demonstrated that the reminder app contributes to a clinically relevant reduction of radiation dermatitis in breast cancer patients, such an app will likely become a useful tool for this group in the near future. When the final results of the DAI-BREAC trial will be available, a limitation of this trial should be considered, namely the fact that standard skin care practices may vary between the contributing centers. This article considered the items recommended to address in the SPIRIT 2013 checklist [16–18].

